#### Relation Between Distributive Shock and Inflammatory Biomarkers

We will study the relationship between alterations in inflammatory and endothelial biomarkers and the changes in SVR, in CO, and the need for fluid replacement. As described above, patients with hypotension and low SVR will be treated with norepinephrine. Therefore, we will analyze potential independent biomarkers and other predictors of SVR adjusted for a dose of norepinephrine.

Vasoplegia might also occur as part of an infection, and CA patients are prone to aspiration and pneumonia after CPR. Therefore, we will calculate modified CPIS daily to describe how many patients develop clinical pneumonia.

Circulatory failure might also be due to structural heart defects (eg, mitral valve insufficiency). An experienced cardiologist will perform echocardiogram daily to assess the heart’s function.

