### Rationale for a New Study

The International Liaison Committee on Resuscitation consensus statement from 2008 acknowledges the lack of knowledge about optimal treatment of PCAS and how to best deliver circulatory support after CA [4].

This protocol describes a study aimed to investigate patients with ROSC after OHCA, regarding (1) characteristics of circulatory failure in PCAS; (2) the endothelial and inflammatory response in PCAS; and (3) the relationship between circulatory failure and the inflammatory and endothelial response in PCAS.

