#### Exclusion Criteria

Exclusion criteria are age <18 years, CA of septic or anaphylactic origin, sepsis within 24 hours before CA, pregnant women, transferred from other hospitals after OHCA, and decision to not initiate life-sustaining therapy after hospital arrival.

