### Censoring

Patients are censored from further follow-up if the patient undergoes acute cardiothoracic surgery or intervention with extracorporeal membranous oxygenation support or a ventricular assist device, at the time of death, if life-prolonging therapy is withdrawn or withheld, or when the patient is transferred to a general ward or another hospital. The reason for censoring is recorded, and all data obtained until censoring will be included in the analysis.

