### Expected Limitations

We recognize some limitations in this protocol. First, the study will obtain information about long-term outcomes and survival. However, this information will only be used to describe the cohort because of the limited number of patients. It would be of interest to study whether circulatory stability and inflammation during PCAS can also predict long-term outcomes, but such analyses should be done in larger cohorts. Second, this study is a single-center study, which limits the generalization of the findings. Third, the included patients are expected to have considerable variability in demographics and comorbidities, in characteristics of the CA, and thus also in PACS complications (eg, infections). Nevertheless, this is presumably the case in all PACS cohorts, and potential findings must be robust to such confounders to be of potential clinical use.

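### Infection is named as a rival cause of vasoplegia and scored daily, but the score's only stated use is a count, so infection-driven biomarker and SVR changes may be misattributed to the post-arrest response

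*Protocol article*

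**What the plan says.** The protocol article's section *Relation Between Distributive Shock and Inflammatory Biomarkers*, within its statistical analysis plan, sets out the analysis in this order:

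- The target: "We will study the relationship between alterations in inflammatory and endothelial biomarkers and the changes in SVR, in CO, and the need for fluid replacement".
- The adjustment: "we will analyze potential independent biomarkers and other predictors of SVR adjusted for a dose of norepinephrine".
- The rival explanation: "Vasoplegia might also occur as part of an infection, and CA patients are prone to aspiration and pneumonia after CPR".
- The response to it: "Therefore, we will calculate modified CPIS daily to describe how many patients develop clinical pneumonia".

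The analysis serves the third aim in *Rationale for a New Study*, which is "the relationship between circulatory failure and the inflammatory and endothelial response in PCAS". *Expected Limitations* lists infections among the complications that will vary between patients and says that "potential findings must be robust to such confounders to be of potential clinical use".

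Modified CPIS and the biomarker samples are both scheduled at inclusion and daily (*Registrations During the Study Period*). Known aspiration during resuscitation is a baseline variable.

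**The concern.** Infection can raise inflammatory biomarkers and lower vascular resistance. It is therefore a possible common cause of the two quantities being related. A patient who develops pneumonia during the five days, with rising cytokines and falling SVR, would add to an apparent biomarker-vasoplegia link in the post-arrest syndrome even if none existed apart from infection.

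The article identifies this problem itself, and the step it draws from it is to report how many patients develop pneumonia. That number describes the cohort. It does not show which patient-days carry the association, or whether the association persists without them. What is at stake is the interpretation of the third aim: whether a biomarker-SVR relation belongs to the post-arrest response or partly to infection that followed it.

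**Working it through.** **Does another provision deal with infection after the arrest?**

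- *Exclusion Criteria* removes "CA of septic or anaphylactic origin, sepsis within 24 hours before CA". Both conditions precede the arrest, so later infection stays in the data.
- *Censoring* begins: "Patients are censored from further follow-up if the patient undergoes acute cardiothoracic surgery or intervention with extracorporeal membranous oxygenation support or a ventricular assist device". The remaining reasons are death, limitation of life-prolonging therapy, and transfer. New infection is not among them.
- *Expected Limitations* sets a standard of robustness but states no adjustment, stratification or sensitivity analysis to test it.

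No stated provision separates the two sources of association.

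**How large could the effect be?** The documents give no infection rate, effect size or SD, so there is no plan figure to reproduce and every input below is an assumption. Let infection affect a proportion p of patient-days, raise a log-biomarker by b and lower SVR by c (residual SDs of 1), with no other link between them. Writing q = p(1-p), the size of the spurious correlation is

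r = q·b·c / √[(1 + q·b²)(1 + q·c²)].

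This increases in q, b and c, so the extremes lie at the ends of the assumed ranges (p 0.2-0.6, b 0.5-1.5, c 0.5-1.0). The largest q is at p = 0.5.

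| p | b | c | Calculation | r |
|---|---|---|---|---|
| 0.2 | 0.5 | 0.5 | 0.04 / 1.04 | 0.038 |
| 0.4 | 1 | 0.5 | 0.12 / √(1.24 × 1.06) | 0.105 |
| 0.4 | 1 | 1 | 0.24 / 1.24 | 0.194 |
| 0.4 | 1.5 | 1 | 0.36 / √(1.54 × 1.24) | 0.261 |
| 0.5 | 1.5 | 1 | 0.375 / √(1.5625 × 1.25) | 0.268 |

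The range is about 0.04 to 0.27. At p = 0.1 with b = c = 0.5, it falls to 0.0225 / 1.0225 = 0.022.

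**Does norepinephrine adjustment remove it?** The formula ignores that adjustment, so a simulation included it. It used 50 patients with one observation each, up to 4,000 runs per scenario, no direct biomarker-SVR effect, and a two-sided 5% test. Norepinephrine rose as vascular tone fell (dose = -0.5 × tone + noise of SD 0.7; measured SVR = tone + 0.5 × dose). Each range runs from the weakest assumed effect (b = c = 0.5) to the strongest (b = 1.5, c = 1).

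| Infection prevalence | False-positive rate, norepinephrine only |
|---|---|
| 10% | 5.4% to 10.2% |
| 20% | 6.2% to 18.8% |
| 40% | 6.4% to 29.9% |
| 60% | 6.7% to 31.6% |

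The mean spurious slope ran from -0.015 to -0.15 SVR units per biomarker unit. Norepinephrine adjustment reduced it only a little: at 40% prevalence with b = c = 1, from -0.145 to -0.121. Adding infection status returned the false-positive rate to 4.6%-5.6% and the slope to within 0.003 of zero in every scenario.

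Two limits apply. Infection status was known without error, which a CPIS would not achieve, and the study's repeated measurements were not modelled.

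**The case against.** The strongest reply is that the article never says the count is the sole use of CPIS, or that norepinephrine is the sole covariate. Its wording on independent biomarkers and other predictors of SVR suggests a multivariable model whose remaining terms are not listed, and CPIS or aspiration could be among them. Covariate lists are commonly left to a fuller document. This stands in part: a reader might infer that CPIS is barred from the models, and the text does not support that. But the article states a purpose for the score, and presents that purpose as its answer to the infection problem. What it states does not answer the problem.

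A reader might also infer that infection-driven changes are certain to be reported as post-arrest inflammation. The documents do not support that either. Infection is named, measured daily and acknowledged as a limitation, and its frequency and effect are unknown. The supportable statement is that misattribution may occur and is not tested for.

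Third, the models in *Patterns Predictive of Deterioration in Circulatory State* are predictive. A biomarker that foresees deterioration partly through infection still predicts it, so the concern should not be extended to them.

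Finally, there are objections to particular remedies. Antibiotics are started on clinical suspicion (*Infection Control*), which inflammation or vasoplegia may itself prompt. Their start is therefore a doubtful covariate or truncation point. With 50 patients, requiring a relation to hold in a restricted subset could discard true relations for lack of power. Both objections stand, and the fix below avoids both remedies.

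**Conclusion.** The point holds for the exploratory analyses of SVR, cardiac output and fluid need. The stated response to infection is descriptive, the one named adjustment does not remove infection confounding, and the article's own robustness standard has no analysis attached to it.

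The size depends wholly on assumptions. The spurious correlation is about 0.04 to 0.27 over the assumed ranges, ignoring norepinephrine. With norepinephrine adjusted for, the simulated false-positive rate runs from near nominal to about 32%. If infection is rare or its effects are weak, the bias is small. This is a worthwhile amendment to an exploratory analysis; it does not invalidate the study or its predictive models.

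**What to change.** For the SVR, cardiac output and fluid-need analyses only, state two sensitivity analyses:

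1. Add daily modified CPIS, or clinical pneumonia, as a time-varying covariate.
2. Restrict to each patient's observations before the first day of suspected pneumonia, with the rule defining that day fixed before analysis.

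Report both beside the main estimate. Word any interpretation specific to the post-arrest syndrome according to whether the estimates are consistent in direction and size, without requiring statistical significance in the restricted set. Keep the descriptive pneumonia count and leave the deterioration models unchanged.

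No new data are needed. The cost is one more model term and fewer late patient-days in the restricted analysis. Separation will be incomplete, because CPIS covers only pulmonary infection and may overlap with post-arrest inflammation; the report should say so.

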## Results

Patient inclusion started in January 2016.

## Discussion

### Rationale for This Study

This study will describe the hemodynamic and inflammatory response characteristics of circulatory failure in PCAS. On the basis of the findings, we will develop a prediction model for risk of circulatory failure in PCAS.

PACS after CA is frequent, and it is strongly associated with mortality after CA [4]. However, there is relatively limited information about the detailed circulatory disturbances in PACS, and principles for circulatory supports are partly transferred from other conditions, in particular, in the treatment of septic shock. Moreover, the expected course (eg, improvement or deterioration) of the circulation is not well understood. The clinical trajectory may be 2-phased: first, a low CO state, followed by a low peripheral resistance state, as previously proposed [20]. Alternatively, it may be one-phased: predominantly caused by either an isolated cardiac failure or an isolated vasoplegia. It is also not established which patients are at a higher risk for circulatory failure in the acute phase of PCAS.

Standard critical illness classification systems, such as SAPS II, SAPS III, acute physiology and chronic health evaluation (APACHE) II, SOFA, or New Early Warning (NEW) scores, are not applicable to describe circulatory changes during the acute phase of PCAS. SAPS and APACHE scores are developed to define risk at admission. SOFA and NEWS scores will reach a ceiling effect and not be able to differentiate between various degrees of circulatory failure in this population. Some researchers have used an extended SOFA circulatory score where 4 further increments are added to the standard circulatory SOFA score [39]. However, this score only includes arterial blood pressure and use of vasopressors, which may not encompass all relevant observations for circulatory stability. Therefore, this study classifies the patients into 3 circulatory groups: *undisturbed, disturbed*, or *severely disturbed circulation* based upon predefined values of mean blood pressure, heart rate, serum lactate concentration, ScvO_2_, use of fluid, vasoactive drugs, and the need for mechanical circulatory devices. Cut-off values were based upon relevant guidelines and clinical practice. All variables were selected because of their known relevance to circulatory failure and because they are easily available during routine monitoring of critically ill patients. More precise measures such as CO or SvO_2_ were not included, as these are usually not obtained in patients after CA.

The clinical trajectories in the acute phase of PCAS are heterogeneous, as seen from the lack of circulatory stability. Such changes can occur immediately after admittance to the ICU or later, at any time, in the clinical course. Thus, the patients are at constant risk. Limited information exists regarding the factors to identify which patients are at the highest risk of imminent clinical circulatory failure. Such factors may include characteristics of the CA episode or clinical observations in the ICU.

This study will establish which factors—demographic, CA-related variables, or clinical observations— will predict circulatory failure and, thus, assess circulatory stability during PCAS.

### Expected Limitations

We recognize some limitations in this protocol. First, the study will obtain information about long-term outcomes and survival. However, this information will only be used to describe the cohort because of the limited number of patients. It would be of interest to study whether circulatory stability and inflammation during PCAS can also predict long-term outcomes, but such analyses should be done in larger cohorts. Second, this study is a single-center study, which limits the generalization of the findings. Third, the included patients are expected to have considerable variability in demographics and comorbidities, in characteristics of the CA, and thus also in PACS complications (eg, infections). Nevertheless, this is presumably the case in all PACS cohorts, and potential findings must be robust to such confounders to be of potential clinical use.

### Conclusions

This study will obtain longitudinally advanced hemodynamic observations with high resolution during the acute phase of PCAS, and it will analyze the details of clinical transitions related to circulatory failure. Additionally, this study will also examine the relationship between inflammatory and endothelial biomarkers and circulatory failure in PCAS.

## Abbreviations

APACHE: acute physiology and chronic health evaluation
CA: cardiac arrest
CCU: coronary care unit
CO: cardiac output
CPC: cerebral performance category
CPIS: clinical pulmonary infection score
CPR: cardiopulmonary resuscitation
EMS: emergency medical service
FiO2: fraction of inspired oxygen
ICU: intensive care unit
IL: interleukin
MAAS: Motor Activity Assessment Scale
MAP: arterial blood pressure
NEW: new early warning
OHCA: out-of-hospital cardiac arrest
PAC: pulmonary artery catheter
PCAS: post cardiac arrest syndrome
PEEP: positive end-expiratory pressure
ROSC: return of spontaneous circulation
SAPS: simplified acute physiology score
SBT: spontaneous breathing trials
SOFA: sequential organ failure assessment
SVR: systemic vascular resistance
TBCS: transitions between circulatory states
